#### 4.2.1 Revised and corrected Stage 2 power and precision calculations

Assumptions underlying the following Stage 2 power calculations include the following:

1. 5% of patients are ineligible for the intervention package (pregnancy, lactation, severe malaria, age <6m (Indonesia) or <1 yr (PNG)).
2. The impact on the risk and rate of infection will be the same across different endemic sites.
3. The mean baseline risk of *P. vivax* recurrence at 6 months is 20%
4. Loss to follow-up in both groups is 10%
5. Alpha = 0.05

During the 12-month pre-implementation period, a total of **17,160** patients with *P. vivax* (mono or mixed infections) presented to the ten study clinics (see Table 1). Assuming 5% of patients are ineligible for enrolment due to pregnancy, lactation or age under 6 months (Indonesia) or 12 months (PNG), this gives an estimated maximum number of patients eligible for recruitment into Stage 2 of **16,300**.

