| 0.5                                                               | 8,150                                   | 135.8                                                           | 12.22                                  | 123.58                                                            | 63.2%                                         |

**Example STATA code:** power pairedm 135.8 111.36, sddiff(15) n(10) alpha(0.05).

Based on previous estimates, 60% of cases of *P. vivax* malaria seen at each clinic are due to relapse and therefore preventable with improved radical cure. We predict the intervention package will reduce the individual risk of relapse by 30%. With anticipated recruitment of 70% of eligible patients, the total predicted sample size in Stage 2 would fall to **11,410** patients receiving primaquine over 12 months of enrolment. Based on this lower predicted enrolment and using the assumptions as above, the predicted absolute reduction in incidence at each clinic would be 17.11 cases per month  $((135.8 \times 0.6) \times 0.3 \times 0.7)$  and resultant power to detect this difference would be **89.3%**.

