### **S2.SE17 - Reduction in individual risk of recurrence**

The power estimates for detecting a reduction in the individual risk of recurrence of *P. vivax* within 6 months from an anticipated study enrolment of **11,410 patients** are presented in Table 3. The number of patients included in the pre-implementation and implementation stages are assumed to be equal (ie a total of 22,820 patients pre and post implementation).

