**Table 3 – Power to detect reduction in the risk of recurrence**

| Proportion of eligible P. vivax malaria patients recruited | Eligible patients over 12 months period | 30% Risk Reduction (HR 0.7) | 20% Risk Reduction (HR 0.8) | 10% Risk Reduction (HR 0.9) |
|-------------------------------------------------------------------|-----------------------------------------|-----------------------------|-----------------------------|-----------------------------|
| 1                                                                 | 16,300                                  | 100%                        | 100%                        | 98%                         |
| 0.9                                                               | 14,670                                  | 100%                        | 100%                        | 97%                         |
| 0.8                                                               | 13,040                                  | 100%                        | 100%                        | 95%                         |
| 0.7                                                               | 11,410                                  | 100%                        | 100%                        | 92%                  |
| 0.6                                                               | 9,780                                   | 100%                        | 100%                        | 88%                         |
| 0.5                                                               | 8,150                                   | 100%                        | 100%                        | 82%                         |

**Example STATA code:** artsurv, edf0(0.2) hr (1,0.7) fp(1) n(22,820) alpha(0.05) nperiod(1) tunit(2) lg(1 2) ldf(0.1;0.1).

A sample size of 11,410 (70% eligible patients) would provide **92% power** to detect a minimum 10% reduction in risk of recurrence and 100% power to detect a 30% reduction in risk of recurrence.

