Individual patient data on the risk of representation with vivax malaria within 6 months to the same health facility site (S2.SE17) will be analysed using survival analysis and visualised with Kaplan-Meier curves. The risk of recurrence will be determined for all patients eligible for PQ treatment and compared between the pre- and post-implementation stages. Multivariable Cox proportional hazards regression will be used to compare these same groups, controlling for age, sex, body weight, calendar time (month), seasonality (captured using splines) and shared frailty of health facility. The validity of the proportional hazards assumption will be assessed visually using Schoenfeld residuals and stratified analyses will be conducted where the assumption is violated.

For S2.EE1, the number and proportion (and 95% Confidence Interval) of patients observed to have a >25% reduction in haemoglobin to a concentration below 7 g/dl will be computed by treatment arm (PQ7, PQ14, PQ8w), and described in summary tables.

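### Table 3's 92% power for a 10% reduction in recurrence (S2.SE17) omits clinic-specific change between periods and any overlap between period and the planned calendar-time adjustment

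*SAP*

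**What the plan says.** S2.SE17 compares the 6-month risk of returning to the same facility with vivax malaria before and after implementation. Section 4.2.1 counts "a total of 22,820 patients pre and post implementation" and obtains Table 3 from an individual-level survival power command. Its inputs are a 20% baseline risk, 10% loss in each group and alpha 0.05, with no cluster, ICC or design-effect term. The text under Table 3 then claims 92% power "to detect a minimum 10% reduction in risk of recurrence and 100% power to detect a 30% reduction in risk of recurrence".

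The listed assumptions include "The impact on the risk and rate of infection will be the same across different endemic sites". They give no between-clinic or clinic-by-period variance.

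For the incidence endpoint S2.SE15, which compares the same ten facilities before and after, the clinic is the unit. The example code under Table 2 is "power pairedm 135.8 111.36, sddiff(15) n(10) alpha(0.05").

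Section 9.2 analyses S2.SE17 by Cox regression, "controlling for age, sex, body weight, calendar time (month), seasonality (captured using splines) and shared frailty of health facility". The Clustering paragraph that follows leaves open whether random effects or robust standard errors by facility will be used for the effectiveness outcomes.

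**The concern.** Every facility contributes both periods, so stable differences between clinics cancel. What limits a before/after comparison in ten clinics is each clinic's own change between periods, for reasons such as local transmission, attendance or stock. Table 3 has no term for that. The shared frailty does not supply one either: a single frailty per facility multiplies the hazard equally in both periods, so it removes baseline differences but not a clinic-specific shift. The month and season terms are not stated to be facility-specific.

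A second gap is between Table 3 and the model it is meant to support. Table 3 is an unadjusted log-rank calculation, whereas the Cox model also adjusts for calendar time. In a before/after design, period is itself a function of calendar time, and depending on how month enters this can cost much of the information.

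At stake are the power claim for a 10% reduction and the width of the S2.SE17 interval. If the interval is too narrow, ordinary clinic drift could be reported as a change in recurrence risk.

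**Working it through.** **1. Reproducing the 92%.** Inputs from Section 4.2.1: 11,410 patients per period, 20% risk, 10% loss, two-sided alpha 0.05 (sidedness is not stated; two-sided reproduces the table). Use exponential hazards with loss as a competing process: λ = −ln 0.8 = 0.2231 and c = −ln 0.9 = 0.1054.

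- Events = n × λ/(λ+c) × (1 − e^−(λ+c)).
- Pre: 11,410 × 0.6793 × 0.2800 = 2,170. Post at HR 0.9 (λ = 0.2008): 11,410 × 0.6558 × 0.2638 = 1,974.
- V = 1/2,170 + 1/1,974 = 0.000967, so SE(log HR) = 0.0311.
- Power = Φ(0.1054/0.0311 − 1.96) = 92%.

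The same method gives 98, 97, 95, 92, 88 and 82% down the HR 0.9 column, as printed.

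**2. Adding clinic-specific change, no calendar term.** Let tau be the SD across clinics of the pre-to-post log HR (assumption; not in the SAP). Split events by the Table 1 shares p_k. The four Timika clinics hold 75% of the volume (12,955/17,160); Σp_k² = 0.180, equivalent to about 5.5 equal clinics.

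- Power when tau is allowed for: v_k = 1/d_pre,k + 1/d_post,k, SE = [Σ 1/(v_k + tau²)]^−½, power = Φ(0.1054/SE − 1.96), or the t counterpart on 9 df.
- Type I error of a facility-intercept-only model: 2[1 − Φ(1.96 × √(V/(V + 0.180 tau²)))].

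| tau | SE | Power HR 0.9, normal | Power HR 0.9, t (9 df) | Type I error, intercept only |
|---|---|---|---|---|
| 0 | 0.0311 | 92% | 85% | 5% |
| 0.05 | 0.0371 | 81% | 72% | 11% |
| 0.10 | 0.0488 | 58% | 49% | 25% |
| 0.20 | 0.0756 | 29% | 24% | 50% |

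Simulation of the intercept-only model gave 11.5% and 26% at tau 0.05 and 0.10. With no clinic-by-period variation, it kept 91–93% power when clinics differed only in baseline risk, so baseline clustering is not the problem.

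For HR 0.8, power is about 96% or more up to tau 0.11, and 83% (normal) or 74% (t) at tau 0.20. For HR 0.7 it is at least about 98% up to tau 0.20.

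**3. Adding a linear calendar month.** Assume 12 months before and 12 after, with month entered linearly. Section 9.2 does not state the form.

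- Over months 1 to 24, the squared correlation between month and the period step is 6²/47.92 = 0.751, so the variance of the period effect is multiplied by 1/(1 − 0.751) = 4.02.
- At tau 0: SE = √(4.02 × 0.000967) = 0.0624 and power for HR 0.9 = Φ(0.1054/0.0624 − 1.96) = 39%. Leaving out the 10% loss gives 41%.
- Type I error with drift (HR 1, so V = 2/2,170 = 0.000922 and 4.02V = 0.00371): replace V by 4.02V in the step 2 formula. This gives about 6% at tau 0.05, 12% at 0.11 and 25% at 0.20.

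The calendar term therefore dilutes the false-positive problem and creates a larger power problem.

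**The case against.** Four points deserve weight.

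- **The SAP does not give tau.** A reader might take 15/135.8 = 11% from Table 2 as the plan's own value and conclude that type I error is about 27% and power about 46%. The documents do not support that. The 15 describes variation in monthly case counts, and the SAP does not settle whether it refers to single months or period means. For single months, Poisson noise in the difference alone would be √(135.8 + 118.69) = 16.0. Episodes per catchment population and recurrence among treated patients are also different quantities. Those figures further leave out the calendar term.
- **Equal impact is a declared assumption.** Section 4.2.1 states it openly. But it concerns the effect of the package. It does not cover background change that differs between clinics, and it does not protect the Cox interval if it fails.
- **The Clustering paragraph offers robust standard errors by facility.** These would capture clinic-by-period variation. That stands in part, but they are an open alternative, Section 9.2 names only the frailty for S2.SE17, and with ten facilities they need a small-sample correction that the SAP does not mention. Section 9.3 says the mixed models allow some heterogeneity in slope and intercept, which appears to be meant for S2.SE15; the S2.SE17 model contains no facility-specific period effect.
- **The calendar term may not be linear.** If month means month of year over complete years, it hardly overlaps with period and step 3 falls away. The SAP does not say which is meant.

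**Conclusion.** The concern holds for the HR 0.9 column of Table 3 and for the S2.SE17 interval. Table 3's arithmetic is correct; what is missing is a variance component and the planned adjustment. The 92% is an upper limit reached only at tau 0 with no calendar overlap. It falls to 81–29% over tau 0.05–0.20 (normal reference), or to about 40% at tau 0 if month enters linearly. Type I error of a facility-intercept model is 11–50% over the same tau range without the calendar term, and about 6–25% with it. All of this rests on assumed values of tau, Table 1 volumes as weights and, for the calendar case, 12+12 months.

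A reader might go further and conclude that S2.SE17 is underpowered altogether. That does not follow. Without the calendar term, power for the 30% reduction that Section 4.2.1 predicts for relapse stays at or above about 98% up to tau 0.20, and a 20% reduction is secure up to about tau 0.11. S2.SE17 is also a secondary endpoint, so the Stage 2 primary result is untouched.

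**What to change.** - **Table 3.** Recompute it for the model actually planned, with its calendar-time and seasonality terms, over a stated range of clinic-by-period SD. Take that SD from, for example, period-to-period variation in recurrence within clinics in the pre-implementation surveillance, not from Table 2's case-count SD. Replace the sentence on a minimum 10% reduction by the smallest reduction that keeps 80–90% power.
- **Section 9.2.** State how calendar month enters the S2.SE17 model. Fix one analysis: either a facility-by-period random effect, or cluster-robust inference with a small-sample correction for ten facilities. Remove the open choice in the Clustering paragraph for this endpoint.

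The cost is SAP wording and a re-run table. The stated power becomes less favourable and the intervals wider; no new data are needed.

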### **S2.PE1 Proportion of patients with *P. vivax* malaria who correctly receive all components of revised case management**

Assuming 70% of patients enrolled into Stage 2 receive all components of the implementation package correctly, the revised Stage 2 sample size of **11,410** patients will give a 95% confidence interval for the true proportion of +/- 0.84%.

### **S2.SE9 Safety and protocol adherence outcomes**

Assuming 1% of patients have a treatment-limiting haemolytic event, the revised Stage 2 sample size of **11,410** patients will give a 95% confidence interval for the true proportion of +/- 0.18%.

## 4.2.2 Original power and precision calculations – now superseded

**Indonesia and PNG combined study**

The Stage 2 implementation study will be conducted at ten health facilities across Indonesia and Papua New Guinea. Based on prior surveillance, we estimate that over 18 months, these health facilities will enrol approximately 16,300 patients with vivax malaria. Improved radical cure of *P. vivax* malaria is expected to reduce the risk of subsequent relapse and therefore reduce the overall incidence of vivax malaria. Across the 10 health facilities, a mean of 91 patients with vivax malaria are expected to be seen each month, 60% ( $n=54.3$ ) of which are predicted to be relapses and therefore feasibly preventable. Assuming that the implementation package in Stage 2 will reduce relapses by 30%, the monthly incidence of *P. vivax* malaria is expected to fall by 16.3 (17.9%) to 74.7 cases per month. With a two-sided alpha of 0.05 and a predicted standard deviation of the mean variation in monthly numbers of vivax malaria of 15 episodes per month, our study would achieve 86% power to detect an 18% reduction in monthly *P. vivax* malaria incidence. Furthermore, assuming 70% of patients receive all components of the implementation package correctly, this sample size will give a 95% confidence interval for the true proportion of  $\pm 0.70\%$ . If 1% of patients are predicted to have a treatment-limiting haemolytic event, this sample size will be powered to determine the true proportion within  $\pm 0.15\%$ .

**Indonesia and PNG standalone studies**

In the unlikely scenario that either Indonesia or PNG will not proceed, the study will become a standalone country study. In this case the sample size calculations are as follows. In a standalone Indonesia study, Stage 1 will occur in the same two health facilities as outlined above. However, we will enrol 800 patients to retain the sample size of the combined study. Stage 1 will still produce a 95% confidence interval for the true proportion needing to stop treatment of  $\pm 1.55\%$ . In Stage 2, the implementation study will be conducted at six health facilities in Indonesia. Based on prior surveillance, we estimate that over 12 months, these health facilities will enrol approximately 10,750 patients with vivax malaria. Across the 6 health facilities, a mean of 60 patients with vivax malaria are anticipated each month, 60% ( $n=36$ ) of which are predicted to be relapses and are therefore preventable. Assuming that the implementation package in Stage 2 will reduce relapses by 30%, the monthly incidence of *P. vivax* malaria is expected to fall by 10.7 (17.9%) to 49.0 cases per month. The Indonesian study alone would retain 80% power to detect a 36% overall reduction in incidence following implementation of the interventions. Furthermore, assuming 70% of patients receive all components of the implementation package correctly, this sample size will give a 95% confidence interval for the true proportion of  $\pm 0.87\%$ . If 1% of patients are predicted to have a treatment-limiting haemolytic event, this sample size will be powered to determine the true proportion within  $\pm 0.19\%$ .

In PNG as a standalone study, Stage 1 will occur in two health facilities, as outlined above, however we will enrol 800 patients to retain the sample size of the combined study. Stage 1 will still produce a 95% confidence interval for the true proportion needing to stop treatment of  $\pm 1.55\%$ . In Stage 2, the implementation study will be conducted at four health facilities in PNG. Based on prior surveillance, we estimate that over 12 months, these health facilities will enrol approximately 5,550 patients with vivax malaria. Improved radical cure of *P. vivax* malaria is expected to reduce the risk of subsequent relapse and therefore reduce the overall incidence of vivax malaria. Across the 4 health

facilities, a mean of 77 patients with vivax malaria are anticipated each month, 60% ( $n=46.3$ ) of which are predicted to be relapses and are therefore preventable. Assuming that the implementation package in Stage 2 will reduce relapses by 30%, the monthly incidence of *P. vivax* malaria is expected to fall by 13.8 (17.9%) to 63.2 cases per month. The PNG arm of the study would retain 80% power to detect a 42% overall reduction in incidence following implementation of the interventions. Furthermore assuming 70% of patients receive all components of the implementation package correctly, this sample size will give a 95% confidence interval for the true proportion of  $\pm 1.21\%$ . If 1% of patients are predicted to have a treatment-limiting haemolytic event, this sample size will be powered to determine the true proportion within  $\pm 0.26\%$ .

Results of the power calculations for the effectiveness endpoints provided above have been confirmed using numerical simulations. A total of 1000 simulated datasets from 10 health facilities, with 18 months of observations and 91 infections per month (in the pre-intervention phase) were generated. Between health-facility variation in the outcome was based on an intra-cluster correlation coefficient of 0.1, and within health-facility variation was assumed to have a standard deviation of the mean variation in monthly numbers of vivax malaria of 15 episodes per month.

## 5 Analysis Objectives

### 5.1. Stage 1 – Preliminary safety and feasibility study

The analysis objectives for Stage 1 are to estimate the proportion of patients with the primary and secondary endpoints (i.e. safety, tolerability and clinical review endpoints) provided in section 2.2.1.

Following accrual of anecdotal evidence of some seemingly erratic haemoglobin results from the SD Biosensor during the early phase of the Stage 1 study, a decision was made to test haemoglobin in duplicate using the bedside HemoCue assay, where available, to ensure patient safety and to provide a means of assessing the reliability of the SD Biosensor. A relevant *post hoc* exploratory endpoint (S1.EE4) has been added to this Statistical Analysis Plan and details of analytical methods are provided below.

Methaemoglobin concentration on days 3 and 7 has recently been proposed as a surrogate marker of primaquine anti-hypnozoite activity (Fadilah I. et al. 20204). Following two reports of adverse events in Papua (low oxygen saturation and elevated methaemoglobin), methaemoglobin began to be measured routinely on days 3 and 7 in Papua midway through Stage 1. Methaemoglobin concentration has therefore been added as a relevant *post hoc* exploratory endpoint (S1.EE5).

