## 2.2 Endpoints

### 2.2.1. Stage 1 – Preliminary safety and feasibility study

All endpoints refer to patients enrolled into Stage 1 treated with daily or weekly PQ.

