#### **Primary endpoints:**

- |        |                                                                                                              |
|--------|--------------------------------------------------------------------------------------------------------------|
| S1.PE1 | Proportion of patients experiencing at least one SAE during treatment.                                       |
| S1.PE2 | Proportion of patients experiencing at least one AESI, SAE or other AE of at least grade 3 during treatment. |

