#### **Secondary endpoints:**

- |        |                                                                                                                                                                                                                                                                                                             |
|--------|-------------------------------------------------------------------------------------------------------------------------------------------------------------------------------------------------------------------------------------------------------------------------------------------------------------|
| S1.SE1 | Proportion of patients with a gastrointestinal AESI during treatment.                                                                                                                                                                                                                                       |
| S1.SE2 | Proportion of patients with an AESI related to haemolysis during treatment.                                                                                                                                                                                                                                 |
| S1.SE3 | Proportion of patients with an AESI related to methaemoglobinaemia during treatment.                                                                                                                                                                                                                        |
| S1.SE4 | Proportion of patients permanently stopping PQ before the end of treatment. 

• Defined as the proportion of all patients enrolled who are given documented advice to permanently stop PQ during scheduled or ad hoc clinical review by a health professional

 |
| S1.SE5 | Proportion of patients receiving correct treatment based on G6PD activity.                                                                                                                                                                                                                                  |

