## 6 Analysis sets/Subgroups

### 6.1. Stage 1 – Preliminary safety and feasibility study

The primary analyses of the endpoints in Stage 1 will include data from all patients enrolled across the four sites in PNG and Indonesia. Secondary analyses of patient-related study outcomes will be conducted overall and for the following prespecified subgroups:

- Patients from Indonesia, Papua New Guinea
- Study site
- Ethnic group
- Patients with G6PD activity >70%, ≥30% to ≤70% and <30%
- Patients prescribed PQ7, PQ14 and PQ8W
- Patients aged <5 years, 5-15 years and >15 years
- Males and females

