For S1.EE5, the distribution of methaemoglobin at baseline, day 3 and day 7 will be presented by treatment arm (PQ7, PQ14, PQ8w) using box and whisker plots. The distribution of methaemoglobin levels at day 7 will be compared between the PQ7 (daily PQ dose of 1mg/kg) and PQ14 (daily PQ dose of 0.5 mg/kg) treatment arms using linear regression after adjusting for baseline haemoglobin concentration, parasitaemia, age, sex, and G6PD enzyme activity level.

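### Routine methaemoglobin testing is described only for Papua and only from midway through Stage 1, but S1.SE3 and the AESI part of S1.PE2 use all enrolled patients with no allowance for this

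*SAP*

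**What the plan says.** - **Testing.** SAP Section 5.1 gives the trigger, "Following two reports of adverse events in Papua (low oxygen saturation and elevated methaemoglobin"), and then the change: "methaemoglobin began to be measured routinely on days 3 and 7 in Papua midway through Stage 1". Papua here means Indonesian Papua, because Sections 3.1 and 6.2 list it separately from PNG.
- **Endpoints.** S1.SE3 is "Proportion of patients with an AESI related to methaemoglobinaemia during treatment". The primary endpoint S1.PE2 is "Proportion of patients experiencing at least one AESI, SAE or other AE of at least grade 3 during treatment".
- **Population.** Section 2.2.1: "All endpoints refer to patients enrolled into Stage 1 treated with daily or weekly PQ". Section 6.1: "The primary analyses of the endpoints in Stage 1 will include data from all patients enrolled across the four sites in PNG and Indonesia". The subgroups in Section 6.1 include "Patients from Indonesia, Papua New Guinea" and study site.
- **Tables.** In Appendix 3, dummy Tables 3 to 5 list methaemoglobinaemia AESIs, serious and non-serious, under the total enrolled, by facility or by treatment. No row gives the number measured.
- **Missing data.** Section 8 prescribes available-case analysis. It does not say whether a patient without a methaemoglobin value is missing or event-free for S1.SE3.
- **S1.EE5.** Under Section 9.1, "the distribution of methaemoglobin at baseline, day 3 and day 7 will be presented by treatment arm", and day 7 values are compared between PQ7 and PQ14 by linear regression. Neither analysis is restricted by site, period or reason for the test.

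**The concern.** A proportion is interpretable when every patient in the denominator had a similar chance of having the event found. Here that chance changed during Stage 1, in one region, in response to events in that region. Elsewhere, and earlier in Papua, the SAP leaves symptom-led detection as the only described route.

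The planned binomial interval reflects sampling error only. It would look precise around a figure that may be too low for a reason unrelated to chance. A reader who sets the PNG row beside the Indonesian row could take a difference in testing for a difference in risk.

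The SAP handles a similar measurement change with more care: after the doubts about SD Biosensor haemoglobin, S1.EE4 was added and stratified by day and country. S1.SE3 and S1.PE2 received no such treatment when the methaemoglobin endpoint S1.EE5 was added.

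For S1.EE5 the issue is mixing. Values taken because a patient had symptoms are likely to be higher than routine ones, and they would enter the same box plots and regression.

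**Working it through.** **Inputs from the SAP.** Stage 1 plans 800 patients, about 500 in Indonesia and 300 in PNG (Section 4.1). The only numerical precision target for Stage 1 concerns stopping treatment: 5%, n = 764, ±1.55%. It reproduces: 1.96 × √(0.05 × 0.95 / 764) = 1.545%. No target is stated for methaemoglobinaemia.

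**Assumptions, not in the SAP.** All 500 Indonesian Stage 1 patients are at Papua sites. Half of them (m = 250) were routinely measured, with a range of 25% to 75% (125 to 375). Let s be the chance of finding a methaemoglobinaemia AESI without routine testing, relative to the chance with it (0 = never, 1 = always). The true risk is the same in both countries.

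**Formulas.** With all enrolled patients as the denominator:
- overall, reported / true = [m + (800 − m) × s] / 800
- Indonesia, reported / true = [m + (500 − m) × s] / 500
- PNG, reported / true = s

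**Overall, reported risk as a share of true risk**

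| s | m = 125 | m = 250 | m = 375 |
|---|---|---|---|
| 0 | 16% | 31% | 47% |
| 0.5 | 58% | 66% | 73% |
| 1 | 100% | 100% | 100% |

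For m = 250 and s = 0.5: (250 + 550 × 0.5) / 800 = 525 / 800 = 0.656.

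**Apparent Indonesia:PNG ratio when the true risks are equal, m = 250**
- s = 0.25: 0.625 / 0.25 = 2.5
- s = 0.5: 0.75 / 0.5 = 1.5
- s = 0.75: 0.875 / 0.75 = 1.17
- s = 1: 1.0

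At s = 0.5 the ratio runs from 1.25 (m = 125) to 1.75 (m = 375).

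**Effect on the interval.** Suppose 5 events, all among the 250 routinely measured. Over all enrolled this is 5/800 = 0.63% (exact 95% CI 0.20% to 1.45%). Among those routinely measured it is 5/250 = 2.0% (0.65% to 4.6%). The first interval is much narrower and excludes the second estimate.

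**Effect on S1.PE2.** A patient with another AESI, an SAE or another AE of grade 3 or more already counts. An undetected methaemoglobinaemia AESI changes the composite only when it is the sole qualifying event, so the effect is smaller than for S1.SE3.

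**Effect of Section 8.** If unmeasured patients are event-free, the table above applies. If they are treated as missing, the denominator shrinks to those measured, and symptom-prompted tests then carry too much weight. The two readings can err in opposite directions.

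**The case against.** The strongest reply is that the bias may be small.
- The SAP does not give the AESI criteria, which may properly sit in the protocol, and objective S1.SO3 speaks of severe methaemoglobinaemia AESIs. If the AESI is defined by symptoms or severity, routine testing of well patients adds few events.
- Detection outside routine testing was possible. The two Papua reports came before routine testing began. Stage 1 planned staff review on days 3 and 7 at its four facilities. The review forms in Appendix 1 carry blue lips, breathlessness and a methaemoglobin percentage, with no country limit shown.

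This stands as a limit on size. It does not show that s = 1, and the plan does not ask for the counts that would show it.

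A reader might go further in four ways that the SAP does not support:
- *The risk is diluted by a known amount, and PNG would show none.* That is the extreme case s = 0.
- *Unmeasured patients are counted as event-free.* The dummy-table layout suggests it, but Section 8 does not say it.
- *Any country difference is an artefact.* Only subgroup estimates are planned, with no between-country test, and a real difference could coexist with unequal testing.
- *The decision to proceed to Stage 2 is undermined.* Section 3.1.1 leaves the progression criteria to the SMC, and Section 11 speaks of the start of Stage 2 in the past tense. What remains at stake is the reporting and interpretation of Stage 1.

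It is also fair to say that S1.EE5 is labelled post hoc and describes measured concentrations, so the denominator problem does not apply to it. The mixing of routine and symptom-prompted values does.

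**Conclusion.** The point holds as one of unequal ascertainment without allowance. With all enrolled patients as the denominator, the pooled S1.SE3 proportion is likely too low, and country and site estimates are confounded by who was tested, unless detection without routine testing was complete. The direction follows from the SAP's own description of the testing.

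The size does not. With 250 of 800 routinely measured, the reported risk lies between 31% and 100% of the true risk. Both the coverage and the location of the Indonesian Stage 1 sites are assumptions, and the AESI criteria could move the answer towards either end.

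S1.PE2 is touched only through patients with no other qualifying event. S1.EE5 is touched through the mixing of values.

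**What to change.** Keep the all-enrolled S1.SE3 estimate as planned, and add to Sections 6.1, 8 and 9.1 and to dummy Tables 3 to 5:

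1. Beside it, the S1.SE3 estimate in patients enrolled at Papua sites after routine measurement began.
2. The number of patients with a methaemoglobin measurement, by site and by period before and after that start.
3. A statement of how unmeasured patients count for S1.SE3 under the available-case rule.
4. S1.PE2 with and without patients whose only event is a methaemoglobinaemia AESI.
5. No country or site comparison of S1.SE3 without the restriction in item 1.
6. S1.EE5 box plots and the PQ7–PQ14 regression limited to patients enrolled after routine measurement began.

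Replacing the all-enrolled estimate with the restricted one would be harder to defend: it would drop PNG from the safety result and may drop the patients whose reports led to the testing.

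The cost is SAP wording and a start-date flag for each site, with no new data. The added estimate has a smaller denominator and a wider interval; in the illustration above, 0.65% to 4.6% against 0.20% to 1.45%.
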